## Abstract

**Background:**

In routine oncological care, the implementation of disease-related quality of life (QoL) is still an open matter. In a complex intervention, a QoL monitoring system including tailored therapeutic options has been designed, implemented, and its effectiveness has been demonstrated in two randomised trials in patients with breast and colorectal cancer. The next step is to extend the usability of the QoL monitoring system for patients with other cancer diagnoses and in other regions. Necessary adaptations include an electronic measurement of QoL and consideration of patient and physician preferences. The present randomised trial investigates the effectiveness of this adapted QoL monitoring system in patients with lung cancer in two regions in Bavaria, Germany.

**Methods:**

In this 2-arm randomised, prospective, pragmatic, multicentre clinical trial with one intervention and one control group, QoL of primary lung cancer patients is assessed with an electronic patient- and physician-oriented QoL monitoring system using the EORTC QLQ-C30 and QLQ-LC29 questionnaires at study entry and at 1, 2, 3, 4, 5, and 6 months during follow-up care. The QoL data of each patient are linked with clinical data from the Bavarian Cancer Registry for the purpose of data analysis. In the intervention group, the results of QoL monitoring are automatically transferred to a QoL profile including 8 dimensions on scales of 0–100 (cut-off “need for QoL therapy” < 50 points). QoL results are obtained in real-time by patients and their treating physicians. To treat QoL deficits, a multi-professional network of healthcare providers is established. In the control group, QoL is also measured, but neither patients nor treating physicians have access to the results. The investigators expect that the proportion of patients in both groups with a need for QoL therapy (< 50 points in at least one dimension of the QoL profile) will be lower in the intervention group than in the control group at the primary endpoint 6 months after study entry.

**Discussion:**

This is the first study investigating the effectiveness of a QoL monitoring system based on patient- and physician-oriented preferences with a high degree of generalisability by including inpatient and outpatient care as well as different study regions.

**Trial registration:**

ClinicalTrials.gov NCT06252233. Registered on February 2024.

## Background

### Background and rationale

Lung cancer is the leading cause of cancer mortality, accounting for approximately 1.80 million deaths worldwide in 2020 [1]. In Germany, in 2019/2020, lung cancer was the most common cause of cancer death in men (22%) and the second most common cause of cancer death in women (16%). In terms of the number of new cases, lung cancer was the second most common tumour location, with 35,890 new cases in German men, and the third most common tumour location in women, with 23,720 new cases. While the incidence rates for men have been declining since the 1990 s, they are increasing for women. In the majority of cases, patients are being diagnosed at an advanced stage [2].

The quality of life (QoL) of lung cancer patients is considerably impaired. Zabora et al. (2001) reported that the level of distress is highest in this patient group than in patients with 13 other common tumour diseases [3]. Over 90% of patients with advanced lung cancer suffer from fatigue, loss of appetite, shortness of breath, cough, and pain [4]. A systematic review investigating the QoL of patients with small cell lung cancer (SCLC) revealed a negatively impaired QoL in most domains compared to that of the general population with physical functioning being most affected [5]. In patients diagnosed with non-small cell lung cancer (NSCLC), Poghosyan et al. (2013) identified pain, dyspnea, coughing, and fatigue as the most common symptoms in the first few months after surgical resection [6]. Such unmet supportive care needs (e.g., physical, emotional, social, psychological, informational, spiritual, and practical needs) are associated with poorer QoL in patients with lung cancer [7].

Therefore, maintaining or improving QoL is an important therapeutic goal in the treatment of patients with lung cancer. Studies investigating the effectiveness of monitoring systems for QoL or adverse events in cancer patients have shown positive effects on QoL [8, 9] and survival [10–12] in routine care. A recent study involving not only health professionals but also patients with colorectal, breast, or gynaecological cancers in their QoL monitoring demonstrated positive effects on physical functioning and self-efficacy during chemotherapy [13]. Thus, QoL monitoring can have positive effects on patient empowerment which can be defined “as the increasing ability of patients to actively understand, participate in, and influence their health status” [14] (p. 1). Accordingly, a systematic review detected positive effects of web-based interventions on patient empowerment compared with usual care [15].

Within our research group, a clinical pathway to improve the QoL of cancer patients has been developed, implemented, and evaluated in a complex intervention [16], including theory development [17], modelling (phase I) [18], and exploratory study (phase II) [19]. Two randomised trials (phase III) showed a significantly better QoL of patients with breast cancer [9] and colorectal cancer [8] receiving systematic QoL diagnosis and therapy during follow-up care. A unique feature of this intervention is that QoL monitoring is embedded in inpatient as well as outpatient care.

The next step is to extend the usability of the QoL pathway so that it can be used by patients with other cancer diagnoses and in other regions (phase IV). Therefore, in the present study, QoL will no longer be measured on a paper-based basis but rather by using an electronic patient- and physician-oriented QoL monitoring system based on previous work [20]. An additional special feature of the intervention is that, in addition to their physicians, patients will also be actively involved in their QoL monitoring and can view the results. The present randomised trial investigates the effectiveness of this adapted QoL monitoring system in patients with lung cancer in two regions of Bavaria, Germany. Additionally, QoL data will be linked with clinical cancer registry data to investigate the feasibility of using the combined dataset to answer relevant medical and therapeutic questions.

### Objectives

The primary objectives are as follows:Assessing the effect of a patient- and physician-oriented QoL monitoring system on the improvement of QoL in lung cancer patientsidentification of benefits and barriers in linking QoL data with cancer registry data

The secondary objectives are as follows:(3)improving the self-efficacy of patients in dealing with lung cancer by actively integrating patients into their QoL monitoring and sensitising them to the various dimensions of their QoL(4)improvement of patient-physician communication(5)evaluation of the acceptance of the QoL monitoring system from the perspective of patients and physicians(6)identification of differences in the use and evaluation of the QoL monitoring system in specific subgroups (e.g., age, sex)

## Methods

### Trial design

The study is a two-armed, randomised, controlled, prospective, pragmatic, multicentre clinical trial with an intervention group and a control group. QoL of primary lung cancer patients will be assessed with an electronic patient- and physician-oriented QoL monitoring system at study entry and after 1, 2, 3, 4, 5, and 6 months of follow-up care. The subjects are randomly assigned (1:1 allocation ratio) to (1) an intervention group with tailored QoL diagnosis and therapy or (2) a control group with routine follow-up care. QoL data of each patient will be linked with clinical data from the Bavarian Cancer Registry for the purpose of data analysis. Thus, it is not necessary to collect patient-, tumour-, or treatment data exclusively for the purpose of this study, but rather existing data which already has been officially registered can be used. This saves a considerable amount of temporal and financial effort. This protocol is compliant with the SPIRIT 2013 reporting guidelines [21].

### Study setting and eligibility criteria

Eight hospitals treating patients with lung cancer in Bavaria, Germany participate in patient recruitment. To achieve adequate participant enrolment there is regular contact between the study unit and the clinicians who are responsible for patient recruitment in the eight hospitals.

The following inclusion criteria apply: (1) primary diagnosis of lung cancer (C33/C34); (2) treatment at one of eight recruiting centres (University Hospital Regensburg, Hospital Barmherzige Brüder Regensburg, Hospital St. Maria Donaustauf, Hospital St. Elisabeth Straubing, Hospital Bayreuth, Sana Hospital Coburg, Hospital Kulmbach, Hospital Bamberg); (3) a time interval between the date of histology and the date of study entry not exceeding 6 months; (4) informed consent (a model consent form can be made available on request).

The exclusion criteria are as follows: (1) unavailability of a study clinician for patient recruitment (e.g., illness); (2) misclassification of the patient in the candidate list (e.g., no primary diagnosis, no lung tumour); (3) refusal of trial participation by the coordinating practitioner; (4) living outside the defined study region (Germany, Bavaria: Upper Palatinate, Lower Bavaria, Upper Franconia); (5) age under 18 years; (6) pregnancy/breastfeeding; (7) inability to fill out the QoL questionnaire (physical, psychological, cognitive, language reasons); (8) refusal of trial participation.

To ensure high external validity [22], there will be no exclusion of elderly patients or according to tumour stage or patient sex. Furthermore, no constraints will be made according to the type of therapy. However, these factors will be accounted for in the data analyses. External validity is also maintained by population-based inclusion of patients from urban and rural areas and by implementing the QoL monitoring system in routine follow-up care. The selection of study participants is shown in Fig. 1.

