### Statistical analyses

All variables will be presented using descriptive statistics (frequencies, percentages, means/standard deviations, medians/interquartile ranges, and various graphical representations). Point estimates will be accompanied by confidence intervals.

The design for the endpoints of primary objective 1 is based on a method of fixed a priori ordered hypotheses [41]. Thus, the second primary endpoint will be analysed only confirmatory at an α of 5% if the null hypothesis of the first primary endpoint can be rejected (*p* < 0.05). This design assures a global alpha of 0.05. The analyses of the primary endpoints (including both the first and second primary endpoints) will be conducted using the Χ^2^-test of independence, setting the level of statistical significance at *p* < 0.05.

Additionally, a multivariable regression analysis in the sense of a sensitivity analysis is planned to adjust for potential risk factors. It is not planned to use imputation to handle missing data in the primary analysis. However, missing data will be accounted for in sensitivity analyses using the following methods: imputation of the last available QoL measurement (last observation carried forward (LOCF) approach); definition of patients with missing data as nonresponders. Analyses will be performed in the intention-to-treat population (sensitivity analysis in the per-protocol population). Statistical tests regarding the secondary endpoints will also use the *p* < 0.05 significance threshold, but all secondary results will be interpreted in an explanatory manner. Secondary analyses will include analyses of covariance (ANCOVAs) using the continuous QoL data as the dependent variable and sex, age, study region, and baseline QoL as covariates.

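### The protocol says tumour stage and type of therapy will be accounted for, but its only named covariate list omits both; the cost is precision and unadjusted chance imbalance, not bias

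*Protocol article*

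**What the plan says.** Under Study setting and eligibility criteria, the protocol article gives its case for external validity: "there will be no exclusion of elderly patients or according to tumour stage or patient sex", and "no constraints will be made according to the type of therapy". The next sentence reads: "However, these factors will be accounted for in the data analyses". The factors meant are therefore age, tumour stage, sex and type of therapy.

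Statistical analyses describes three layers:

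- The primary endpoints are compared by an unadjusted chi-square test.
- For sensitivity, "a multivariable regression analysis in the sense of a sensitivity analysis is planned to adjust for potential risk factors". These factors are not listed.
- The secondary ANCOVAs are run "using the continuous QoL data as the dependent variable and sex, age, study region, and baseline QoL as covariates".

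Under Randomisation and blindness, allocation is 1:1, in blocks, stratified by gender and centre. Tumour and treatment data are to come from the Bavarian Cancer Registry, linked patient by patient. Trial design says that for this reason "it is not necessary to collect patient-, tumour-, or treatment data exclusively for the purpose of this study", and Clinical cancer registry data gives diagnoses and therapy procedures as examples of what is obtained.

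**The concern.** The eligibility section commits to four factors. The one model whose covariates are written out covers two of them, and its list is closed: it is not introduced as a set of examples. The two left out, stage and therapy, are likely to be strongly related to how quality of life develops over six months in lung cancer. Neither is a stratification factor, so the design does not balance them beyond what simple chance provides. Baseline QoL is in the ANCOVA, but patients with similar baseline profiles can have different expected courses depending on stage and planned treatment.

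At stake is the efficiency of the adjusted analyses and how they will be read. If the arms differ by chance in the share with advanced disease, the ANCOVAs as specified cannot correct for it. If stage enters only later, through the open list in the sensitivity regression, that choice may look data-driven.

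**Working it through.** **1. Promise against named models.**

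| Factor in the eligibility section | Stratum | Secondary ANCOVA | Sensitivity regression |
|---|---|---|---|
| Age | no | yes | not stated |
| Sex | yes | yes | not stated |
| Tumour stage | no | no | not stated |
| Type of therapy | no | no | not stated |

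No section names an analysis that contains stage or therapy.

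**2. The plan's own figure.** Inputs from Sample size: 45% against 25%, α 5% (taken as two-sided), power 80%. The pooled rate is 0.35.

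n = [1.960·√(2·0.35·0.65) + 0.842·√(0.45·0.55 + 0.25·0.75)]² / 0.20² = (1.322 + 0.555)² / 0.04 ≈ 88.1, rounded up to 89 per arm.

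This reproduces the stated 89 (power 0.804). It uses no covariates, so the point does not touch it.

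**3. Size of a chance imbalance in stage.** The documents give neither the stage mix nor responder rates by stage, so both are assumed. With 89 per arm and advanced share p, the SD of the between-arm difference in share is √(2p(1−p)/89):

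- p = 0.5: 7.5 points
- p = 0.6: 7.3 points
- p = 0.7: 6.9 points

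**4. Effect on the responder difference.** Multiply this SD by the assumed gap in responder rate between early and advanced disease, keeping control patients at 25% overall. The SD of the difference from all causes is about √(2·0.25·0.75/89) = 6.5 points under no effect.

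| Advanced share | Responders, advanced / early | SD of shift from imbalance | Share of variance |
|---|---|---|---|
| 50% | 15% / 35% | 7.5 × 0.20 = 1.5 points | (1.5/6.5)² ≈ 5% |
| 50% | 10% / 40% | 7.5 × 0.30 = 2.3 points | about 12% |
| 70% | 15% / 48% | 6.9 × 0.33 = 2.3 points | about 12% |

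An unlucky two-SD imbalance would move the estimate by 3.0 to 4.6 points, or 15% to 23% of the planned 20-point effect. The variance shares are before any overlap with baseline QoL, which is already in the ANCOVA and would reduce them.

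**5. Is the unadjusted test biased?** The same three scenarios were simulated, 200,000 trials each, with stage ignored. The mean error in the risk difference was at most 0.0001 in absolute value. Type I error was 4.8% to 5.0%. With a true 20-point effect, the mean estimate was 0.200 and power about 0.81. Omitting stage leaves the primary test valid.

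**The case against.** The strongest reply is that no contradiction is proven. The eligibility section does not say that every analysis will adjust for every factor. The sensitivity regression follows directly on the primary tests, its covariates are open, and it could hold stage and therapy. A covariate list for such a model is commonly left to the analysis plan, which is not shown. This stands for the regression. It does not stand for the ANCOVA, whose list the article does fix, without the two factors.

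Three stronger readings are tempting and are not supported:

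- A reader might infer that the trial has no data on stage or treatment. Trial design and Clinical cancer registry data say that tumour and treatment data are taken from the registry instead of being collected a second time.
- A reader might infer that disease course biases the treatment effect. Allocation is randomised. The shifts in step 4 are part of the ordinary sampling error that the test already allows for.
- A reader might infer that the first primary objective hinges on the second, because the background section sets out "to investigate the feasibility of using the combined dataset to answer relevant medical and therapeutic questions". The primary endpoint and its test use QoL data only. If linkage failed, only adjusted analyses that use registry variables would suffer, and no section reports that linkage is late or incomplete.

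**Conclusion.** The point holds as a mismatch of wording with a modest statistical cost. The protocol says stage and type of therapy will be accounted for; the one covariate list it gives leaves both out, and the other adjusted model does not say. The consequence is lost precision and uncorrected chance imbalance in the secondary and supportive analyses. The primary chi-square test, its error rate and the 220 patients are unaffected.

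Under the assumed stage mixes and prognostic gaps, stage accounts for about 5% to 12% of the variance of the responder difference. The corresponding gain for the continuous QoL scores cannot be computed from the article. It depends on how strongly stage predicts month-6 QoL once baseline QoL is known. The size therefore rests on assumptions; the omission from the named list does not.

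**What to change.** In Statistical analyses, add two covariates to the ANCOVA list and name the same two in the multivariable sensitivity regression:

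- tumour stage at diagnosis, from the linked registry data;
- treatment intent or type as planned at study entry.

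State that therapy received after randomisation is not used as a covariate, since the intervention could influence it. The analyses would then match the eligibility section.

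The cost is small: a few degrees of freedom, and adjusted analyses that depend on complete linkage. The article does not say whether the registry records planned treatment, so the source of that variable should be confirmed. Adding fields to the recruitment form is not a good substitute. Recruitment began in February 2024, so patients already enrolled would be missed; the form's contents are not described; and the fields would duplicate data the design takes from the registry.

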**Fig. 1 Fig1:**
[figure not shown]
Selection of patients

During follow-up care patients are treated by their coordinating practitioners (CPs), who are defined as those physicians who care for the lung cancer patients after hospital stay in the outpatient setting (oncologists, pneumologists, internists, general practitioners).

### Randomisation and blindness

Subjects who meet inclusion criteria but none of the exclusion criteria are randomly assigned to the intervention or control group (1:1 allocation ratio) with the underlying parameters block randomisation and stratified randomisation with the strata gender (female/male) and centre. Random lists were generated by the Center for Clinical Studies (CCS) using the software SAS 9.4. Based on these random lists of digits, a coworker of the Tumor Center Regensburg (TCR), otherwise not involved in the trial, creates paper cards for each of the six recruiting centres specifying the study group for male and female participants and inserts them in serially numbered opaque, sealed envelopes. This stack of envelopes is kept in a locked safe at the study coordination unit of TCR, which is separated from the study research unit of UR/TCR in terms of space, organization and personnel to which only the two study coordinators have access. This procedure ensures that study coordinators who are responsible for randomisation of study patients are kept blind to the randomisation sequence. The eligibility of the study patients is determined by study clinicians in each of the six recruiting centres. If all criteria are fulfilled and the patient has given informed consent the study clinician sends the recruitment document to the study coordination unit (TCR) by fax. The exact date and time of fax entry determine the order in which patients from each centre are randomised.

The recruiting clinicians who determine study eligibility are blinded to the randomisation sequence. CPs and patients cannot be blinded to allocation for practical reasons because the intervention requires that intervention group patients and their CPs have access to the results of QoL monitoring. However, the study staff conducting the patient and physician evaluations after 3 and 6 months will be blinded to the condition of allocation.

### Patient- and physician-oriented QoL monitoring system

In order to provide a comprehensible and manageable QoL monitoring system for both patients and physicians, we aim to focus on what matters most to both patients and physicians, i.e., to concentrate on the most relevant QoL dimensions for both study groups, respectively. Therefore, prior to the initiation of the RCT we developed and performed two separate discrete choice experiments (DCEs) to elicit and compare patients’ and physicians’ preferences for relevant QoL dimensions during lung cancer treatment. DCEs are increasingly used in the healthcare context to inform on preferences for healthcare services such as treatment choices [23]. DCEs are a stated preference method in which (survey) data are used to elicit the preferences of patients, physicians, and others based on a series of hypothetical choice scenarios [24].

Therefore, our study used a mixed methods approach. First, we performed two systematic search procedures on Medline (via PubMed) and the Cochrane Library to identify literature that aimed to identify and evaluate the importance of QoL dimensions during lung cancer treatment from the perspective of both patients and physicians. Second, we qualitatively surveyed 16 randomly selected lung cancer patients and 16 physicians to learn more about the importance of the identified QoL dimensions during lung cancer treatment. The respondents were sent a short survey via postal email before conducting semi-structured interviews regarding the importance of the identified QoL dimensions. The aim of the semi-structured interviews was to explore in greater depth the stated preferences, to determine the most relevant QoL dimensions as well as corresponding levels, to clarify the wording, and to evaluate the comprehensibility of hypothetical choice tasks for the DCE.

Third, we developed one online-based survey version of the DCE for each study group. Both survey instruments were similar and consisted of four parts. First, respondents were presented with relevant QoL dimensions (e.g., pain, shortness of breath, emotional impairment) as well as short descriptions and were asked to rate each QoL dimension on a 1–5 scale (1 = not all important; 5 = very important). Furthermore, we asked both patients and physicians to select the single most important QoL dimension during lung cancer treatment. Second, all respondents responded to the DCE survey block. Here, both DCE experiments were designed using Sawtooth Software Lighthouse Studio 9.14.2. Thereby, DCEs perform pairwise comparisons of hypothetical alternatives (i.e., differently configured health statuses during lung cancer treatment) and ask respondents to choose between them. We used full profile designs (i.e., each choice set included all six QoL dimensions) and the balanced overlap method to achieve standard errors below 0.05 for main effect utilities and 0.10 or smaller for interaction effects and the highest D-efficiency score [25]. We designed the choice sets in both surveys as forced-choice tasks (i.e., respondents had to choose one of two hypothetical health status by making trade-off decisions). As stated above, health statuses differed in six attributes with three levels each following current DCE guidelines [26]. Third, we evaluated both the clarity and comprehensibility of different QoL monitoring system designs. Therefore, we presented different ways of presenting QoL development over time based on international practices. Fourth, we asked for general sociodemographic information (e.g., age, gender) as well as treatment-related information. The questionnaire was pilot tested for clarity and understanding with 8 lung cancer patients and 9 physicians and was slightly modified accordingly. Both surveys were conducted online, i.e., patients and physicians were contacted via email or received a paper-based flyer that contained information about the survey and a link to participate online (web-based survey). Based on the results of both DCE experiments, we selected the eight most relevant QoL dimensions for inclusion in our QoL monitoring system and listed each QoL dimension depending on its importance.

